## Abstract

**Background:**

Despite compelling evidence of the benefits of treatment and well-accepted guidelines for treatment, hypertension is controlled in less than one-half of United States citizens.

**Methods/design:**

This randomized controlled trial tests whether explicit financial incentives promote the translation of guideline-recommended care for hypertension into clinical practice and improve blood pressure (BP) control in the primary care setting. Using constrained randomization, we assigned 12 Veterans Affairs hospital outpatient clinics to four study arms: physician-level incentive; group-level incentive; combination of physician and group incentives; and no incentives (control). All participants at the hospital (cluster) were assigned to the same study arm. We enrolled 83 full-time primary care physicians and 42 non-physician personnel. The intervention consisted of an educational session about guideline-recommended care for hypertension, five audit and feedback reports, and five disbursements of incentive payments. Incentive payments rewarded participants for chart-documented use of guideline-recommended antihypertensive medications, BP control, and appropriate responses to uncontrolled BP during a prior four-month performance period over the 20-month intervention. To identify potential unintended consequences of the incentives, the study team interviewed study participants, as well as non-participant primary care personnel and leadership at study sites. Chart reviews included data collection on quality measures not related to hypertension. To evaluate the persistence of the effect of the incentives, the study design includes a washout period.

**Discussion:**

We briefly describe the rationale for the interventions being studied, as well as the major design choices. Rigorous research designs such as the one described here are necessary to determine whether performance-based payment arrangements such as financial incentives result in meaningful quality improvements.

**Trial Registration:**

http://www.clinicaltrials.govNCT00302718

## Background

Despite compelling evidence of the benefits of treatment, hypertension is controlled in less than one-half of United States (US) citizens with the disease [1]. Inadequate blood pressure (BP) control results in excess morbidity and mortality from cardiac, renal, and peripheral vascular disease [2]. While some cases of poor BP control relate to patients' compliance with treatment, there is significant under-treatment of hypertension on the part of physicians. In one study, hypertension patients received less than 65% of care that was indicated for this condition [3].

Under-treatment of hypertension is puzzling, because good evidence exists about the efficacy of antihypertensive medications. Despite widespread dissemination of guidelines for treatment of hypertension (including the Seventh Report of the Joint National Committee (JNC 7) on Prevention, Detection, Evaluation, and Treatment of High Blood Pressure), and widespread comparative effectiveness trials such as the Antihypertensive and Lipid-Lowering Treatment to Prevent Heart Attack Trial (ALLHAT) [4], translation into clinical practice has been incomplete [5].

Awareness of barriers to such clinical research translation has raised enthusiasm about using novel methods, such as financial incentives, to overcome them [6]. A number of pay-for-performance programs have been implemented in the United Kingdom (UK) and the US [7,8]. However, research evidence of effectiveness of pay-for-performance programs, particularly randomized trials, is limited [9,10]. Using a cluster randomized controlled trial (RCT), we are testing the effect of explicit financial incentives to promote the translation of guideline-recommend care for hypertension into clinical practice and thereby improve BP control in the primary care setting. This trial addresses the needs of policy makers, payers, physicians, administrators, and others for information about a clinically relevant intervention in routine practice. We are not aware of other ongoing randomized trials of pay for performance directed at physicians and provider groups [11].

### Design of trial

Because our goal was to evaluate the impact of financial incentives on individual physicians as well as primary care provider groups, we implemented a cluster randomized controlled design and clustered at the facility level [12].

### Design of incentives

Should individuals, groups, or some combination receive financial incentives for their performance? One could anticipate that with group- or practice-team-level incentives, individual physicians would not capture the full returns on their individual effort to improve the quality of their care. Traditional economic theory suggests that the potential for some physicians to 'free-ride' on the efforts of others may lead many to reduce their individual efforts [10,13]. Conversely, the problem with rewarding individuals, but not the individual's team or group, is that cooperation among the group is not necessarily encouraged. Moreover, group incentives may be important in supporting and rewarding infrastructure improvements to the healthcare delivery system. Studies evaluating the chronic care model suggest that multi-disciplinary teams produce better patient outcomes [14,15]. Yet, traditional fee-for-service payment models create disincentives for making organizational changes in care delivery [15,16]. Thus, theory suggests the potential for group-level incentives to support organizational and team-based efforts to improve quality, but it is not yet known how these effects compare to individual-level incentives.

The design of incentives for quality also raises the question, what should we reward? Would incentives targeting processes (*i.e*., what clinicians do) or outcomes (*i.e*., what ultimately happens to patients) be expected to produce the highest quality? Of course, the best process-of-care measures are those for which there is evidence that better performance leads to better outcomes. But it is important to note that process-of-care measures may be more sensitive to quality differences than are measures of outcomes, because a poor outcome does not necessarily occur every time there is a quality problem. Furthermore, outcomes are often dependent upon events that are outside of the control of the clinician. For example, one can prescribe guideline-recommended medications, but if the patient is not able to adhere to these medications, the BP may not be controlled. One theoretical problem with using incentives solely based upon process-of-care measures is that physicians may attempt 'gaming' and focus solely on the measure (*i.e*., use of a guideline-recommended medication), while ignoring the intended outcome, which is the attainment of a target BP.

To avoid the problems associated with the exclusive use of process-of-care or outcome measures described above and to dampen the gaming incentive, both a process-of-care measure (use of guideline-recommended medications in patients who have no other compelling indications) and an intermediate outcome measure (achievement of the JNC 7 BP goal) will be used. This approach may avoid the pitfalls of process-of-care measures alone that can encourage gaming, while avoiding the disadvantage of basing incentives solely on outcomes that may be relatively rare or difficult to achieve and somewhat beyond the control of the provider. Thus, a combined approach potentially capitalizes upon the advantages and complementary nature of both types of quality-of-care measures [9]. The design of our trial reflects the following logic: other things being equal, process-based incentives will create stronger incentives for improvement in process (which the physician can directly control); similarly, process-based incentives may also produce better outcomes (assuming that the processes being incentivized improve outcomes). We believe that combining outcome-based with process-based incentives has the potential to produce even greater quality improvement than process measures alone [17].

A third design question is whether the incentive payments should be distributed according to relative performance (*i.e*., the participant's percentile ranking compared to peers) or absolute performance (*i.e*., strictly according to performance relative to the same standard)? The former approach may be problematic because participants cannot directly control the behavior or outcomes of others on whom a relative comparison is based. The latter approach rewards behavior that the individual or group can directly control [10,13]. Therefore, we designed our incentives to reward participants each time they provided guideline-recommended medications and/or their patient met the guideline-recommended BP threshold or, in the absence of controlled BP, the participant appropriately responded to uncontrolled BP [17].

In this article, we describe the methods used to assess the effects of physician- and group-level financial incentives on processes and outcomes of care for outpatients with hypertension.

## Methods/design

### Study objectives

The goals of this study were to: determine the effect of physician-level financial incentives on processes and outcomes of care for outpatients with hypertension; assess the impact of group-level financial incentives; ascertain whether there are additive effects of physician- plus group-level financial incentives; evaluate the persistence of the effect of financial incentives; and identify any unintended consequences of these explicit financial incentives.

### Study design

This study is a four-arm cluster RCT of individual physician incentives, group-level financial incentives, and performance audit and feedback to improve the translation of guideline-recommended care for hypertension in the primary care setting. Participants at study sites randomized to one of the three intervention arms earned either physician-level, group-level, or physician- and group-level incentives (combined incentive arm). Both intervention and control arm (no incentives) participants received audit and feedback reports.

### Study sites and constrained randomization

We partnered with five Veterans Affairs (VA) regional networks to implement the study. Within these networks, hospital-based VA outpatient clinics that could conduct human subjects' research and had eight or more eligible primary care physicians were potential study sites. Of the 22 potential study sites, only 12 met the requirements for study implementation: hospital director approval; Institutional Review Board (IRB) and VA Research and Development (R&D) approval; having a credentialed individual willing to serve as the site's PI; and having at least five consented physician participants at time of randomization. We stratified these 12 study sites on the following characteristics expected *a priori *to be associated with responses to financial incentives and the study outcomes of interest: teaching status, geographic location, participation in the ALLHAT study [4] (a very large trial of various medications used to treat hypertension in both VA and non-VA settings that included intensive education regarding hypertension control and use of evidence-based hypertension treatment at participating sites), and the degree of clinic geographic proximity within the primary care setting at each study site. We identified a hospital as a teaching facility if it was listed in the Association of American Medical College's (AAMC) Council of Teaching Hospitals (COTH) directory or if the American Medical Association's (AMA) Fellowship and Residency Electronic Interactive Database (FREIDA) listed the VA facility as having a 'major' affiliation with a medical school. To determine geographic region, we used US Census Bureau information to identify the corresponding Census Division for each site. Study site investigators provided clinic layout information, and we designated sites as being integrated if the layout was amenable to group cohesion (*e.g*., the primary care clinic offices were located on the same floor at the study site).

We randomized at the cluster (facility) level. To ensure that facilities of the same type would not be concentrated in the same arm, we employed the following constraints: all non-teaching facilities could not be in the same arm; all non-ALLHAT sites could not be in the same study arm; no arm could have two sites from the same geographic location; and at least two sites per arm had to meet the criteria for geographic integration (Figure 1). Using SAS version 9.1.3 (SAS Institute Inc, Cary, NC), a data analyst on the study team who was not involved in the processes of site selection or subject recruitment assigned a uniform random number to each of the possible allocations and selected the allocation sequence with the highest random number. Table 1 lists the characteristics of the study sites.

**Figure 1 F1:**
[figure not shown]
**Randomization schematic**. ALLHAT = Antihypertensive and Lipid-Lowering Treatment to Prevent Heart Attack Trial; VA = Veterans Administration. *Enrolled up to seven primary care physicians at each study site. †Enrolled up to 15 non-physician participants (*e.g*., nurses and pharmacists) at each study site.

**Table 1 T1:** Study site characteristics

VA hospital	City, State	Teaching facility*	US Census Division	ALLHAT study site	Primary care geographic integration†
VA Boston HCS	Boston, MA	X	New England		X

Providence VAMC	Providence, RI	X	New England	X	X

VA Connecticut HCS	Newington, CT		New England		X

Charlie Norwood VAMC	Augusta, GA	X	South Atlantic	X	X

Ralph H. Johnson VAMC	Charleston, SC	X	South Atlantic	X	X

Birmingham VAMC	Birmingham, AL	X	E. South Central		X

Aleda E. Lutz VAMC	Saginaw, MI		E. North Central		

John D. Dingell VAMC	Detroit, MI	X	E. North Central	X	X

G.V. (Sonny) Montgomery VAMC	Jackson, MS	X	E. South Central	X	

Michael E. DeBakey VAMC	Houston, TX	X	W. South Central	X	

Oklahoma City VAMC	Oklahoma City, OK	X	W. South Central	X	X

Minneapolis VAMC	Minneapolis, MN	X	W. North Central	X	

ALLHAT = Antihypertensive and Lipid-Lowering Treatment to Prevent Heart Attack Trial; HCS = healthcare system; US = United States;

VA = Veterans Administration; VAMC = Veterans Affairs Medical Center

***Designated as a teaching facility if the facility was either listed in the Association of American Medical College's (AAMC) Council of Teaching Hospitals (COTH) directory or if the American Medical Association's (AMA) Fellowship and Residency Electronic Interactive Database (FREIDA) database listed the VA facility as having a 'major' affiliation with a medical school.

†Designated as geographically integrated if the primary care clinic layout was amenable to group cohesion (*e.g*., the primary care clinic offices located on the same floor at the study site).

### Power and sample size

The anticipated effect sizes were based upon a systematic review of financial incentives in healthcare [9]. In that review, the range of increases in performance using physician-level incentives was 5.9% to 25.3%, most of which were for preventive services such as immunizations. Because this study assesses treatment of a chronic disease requiring multiple types of interventions (*i.e*., medications, counseling, monitoring, lifestyle modification), rather than a single immunization, the increase in performance is anticipated to be somewhat less than those trials at the high end of this range.

The sample size calculation must take into account several factors. First, this is a cluster design, randomized at the facility level. Second, there is a measurement error associated with estimating each physician's proportion, because we can only sample a finite number of patients per physician. Finally, there must be a correction for multiple comparisons because we are testing two effects and an interaction. The sample size computation uses the non-central t-distribution and is based on a SAS^® ^program from Donner and Klar [18]. An iterative solution is required because the number of degrees of freedom depends on the sample size. The variance in measurements is the sum of the variance between hospitals, the remaining variation between physicians and the error variance of the measurement. Estimates of the variance between hospitals and the variance between physicians were obtained from pilot data. The error variance of measurement of the physician's proportion was calculated from the binomial distribution. Using these data, we estimated values of the intraclass correlation of 0.39 for appropriate medication and 0.14 for BP control.

We provide power calculations for the process and outcome measures. We calculated effect sizes for various values of the difference in percentage use of appropriate medication and BP control we could detect between the study arms with 80% power using a two-sided t-test with 95% significance. Greater increases in power result from increasing the number of clusters than by increasing the number of cases within clusters [18]. However, it is much more difficult and costly to recruit more hospitals. We chose to use three hospitals per study arm with five physicians per hospital and 40 patient charts per physician. We determined that we could detect a difference of 17 percentage points between the mean proportions of appropriate medications in the arms, for an effect size of 1.59. Similarly, for BP control, we determined we could detect a difference of 15 percentage points between the mean proportions in the study arms for an effect size of 1.30.

We adjusted the sample size to account for anticipated physician participant attrition. Using VA physician workforce planning data, we estimated 5.8% would leave VA employment during the study. We adjusted our initial sample size, five physicians per site, to seven per site to account for attrition using the formula proposed by Lachin [19], defined as 1/(1-R)^2 ^where R is the drop-out rate.

### Baseline characteristics of study participants

Primary care physicians who worked at least 0.6 full-time equivalents (approximately three days per week related to clinical activities) or had a panel size of at least 500 patients were eligible to participate. Research assistants on the Houston coordinating center study team obtained informed consent from at least five eligible participants (see Power and sample size section) at each study site prior to randomization. We sought to avoid coercion by informing the individuals that participation was strictly voluntary, that their decision to participate would not impact their employment status, and that their supervisors and other hospital officials would not have access to their performance data. Following randomization of study sites to study arms, we continued to consent eligible physician participants as necessary to meet our recruitment goal of seven physicians per site (see Power and sample size section). We enrolled a total of 83 physicians from 12 VA hospitals. At two sites, more than seven eligible physicians consented for the study, so we randomly chose seven among those who consented.

All enrolled physicians in a hospital were placed in the same study arm. At the six study sites randomized to the group-level incentive, the physicians invited up to 15 non-physician colleagues, either other clinicians (*e.g*., nurses and pharmacists) or administrative support staff (*e.g*., clerks) or both, to participate. Research assistants on the Houston coordinating center study team obtained informed consent from 42 non-physician participants. Table 2 lists the demographic characteristics of the physician and non-physician primary care personnel who were enrolled at the start of the intervention period.

**Table 2 T2:** Characteristics of physicians and non-physician primary care personnel enrolled at the start of the intervention

Characteristic*	Primary care physicians (n = 83)	Non-physician personnel (n = 42)
Male, n (%)	45 (54.2)	6 (14.3)

Age at start of study, mean (SD), *y*	46.5 (7.8)	48.7 (8.7)

Race/ethnicity, n (%)		
White	35 (42.2)	24 (57.1)
Black	6 (7.2)	12 (28.6)
Asian	34 (41.0)	3 (7.1)
Hispanic	4 (4.8)	1 (2.4)
Other†	3 (3.6)	2 (4.8)
Unknown‡	1 (1.2)	0

Board certified, n (%)	76 (91.6)	N/A

Primary specialty internal medicine, n (%)	71 (85.5)	N/A

Trained in a subspecialty/secondary specialty, n (%)	18 (21.7)	N/A

Years practicing since residency completion, mean (SD)	12.6 (7.8)	N/A

Proportion of professional time spent delivering patient care, mean (SD)	0.89 (0.13)	0.86 (0.20)

Role in patient care delivery, n (%)	N/A	
Licensed practical nurse	N/A	10 (23.8)
Medical support assistant	N/A	3 (7.1)
Pharmacist	N/A	2 (4.8)
Physician assistant or nurse practitioner	N/A	5 (11.9)
Registered nurse	N/A	16 (38.1)
Registered nurse case manager or care coordinator	N/A	6 (14.3)

*****Data collected as part of the participant demographic questionnaire conducted following the informed consent discussion.

†Other includes participants that described themselves as Native Hawaiian/Other Pacific Islander, American Indian/Alaska Native, or belonging to more than one race/ethnicity group.

‡Participant declined to answer.

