### Interventions

#### Provider education

Between February and April 2008, we provided all participants with the current JNC 7 hypertension guidelines during live educational webinars presented by a cardiologist and an internist. At the sessions, participants learned their study arm assignment. Participants in the intervention arms received information about the magnitude and criteria for the incentives.

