While our study design has numerous strengths, we must acknowledge some limitations. First, as part of the VA Healthcare Personnel Enhancement Act of 2004 (implemented in 2006) [28], the VA healthcare system instituted a new payment system that includes performance pay based on the accomplishment of specific clinical quality goals and objectives which may be established at the local, network, or national level. However, although this program provides financial incentives for improvements in quality of care, the specific measures (*i.e*., hypertension control, diabetes management, colorectal cancer screening) for which payments are given have not been implemented uniformly across VA facilities. In addition, VA performance pay encompasses a wide array of measures, while our incentive focuses solely on management of hypertension, thus maximizing the effect of our intervention. Further, by using a RCT design, we limit the likelihood of confounding by other concurrent quality improvement programs. Second, the VA has an extensive system of clinical reminders (*i.e*., use of thiazide diuretics in patients with hypertension or use of aspirin in patients with ischemic heart disease) designed to promote the provision of guideline-recommended care. However, while the VA has implemented a variety of quality improvement strategies, our pilot data indicate that there remains room for further improvement. Third, although the VA healthcare system cares for few women patients, the subjects of this study are physicians. There is little reason to believe that the effect of a financial incentive to a physician would result in different treatment of a woman or a man with hypertension. Thus, findings from this study will be relatively generalizable to budgeted systems and staff-model health maintenance organizations (HMOs) that serve many millions of patients, to Centers for Medicare and Medicaid Services (CMS) with 40.5 million beneficiaries, and indirectly applicable to other healthcare delivery models. Finally, it is possible that there may be a 'volunteer effect' among participants. For example, physicians with a bias toward use of financial incentives may have been more likely to participate in our study. However, we expect that the randomized control design of our study will limit the effect of this potential source of bias.

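### Some physicians were consented after their site was randomised, so the statement that randomisation limits the volunteer effect covers late recruits only if allocation was concealed from them and from recruiters

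*Protocol article*

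**What the plan says.** All references are to the Protocol article.

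- **Before randomisation.** Study sites and constrained randomization makes it a site requirement to be "having at least five consented physician participants at time of randomization". Baseline characteristics of study participants agrees: research assistants "obtained informed consent from at least five eligible participants (see Power and sample size section) at each study site prior to randomization".
- **After randomisation.** The same section continues: "Following randomization of study sites to study arms, we continued to consent eligible physician participants as necessary to meet our recruitment goal" of seven per site. It then reports: "We enrolled a total of 83 physicians from 12 VA hospitals". It adds: "At two sites, more than seven eligible physicians consented for the study, so we randomly chose seven among those who consented". It does not say how many of the 83 consented before or after allocation, overall or by arm.
- **Who recruited.** "Research assistants on the Houston coordinating center study team obtained informed consent" from physicians at every site. The same team consented the 42 non-physicians, who were recruited only at the six sites with a group incentive, on the invitation of the physicians there.
- **Who knew the arm.** Of the webinars held from February to April 2008, Provider education says: "At the sessions, participants learned their study arm assignment". The analyst who drew the allocation took no part in recruitment. The only masking described is that of the chart abstractors (Data collection).
- **The reassurance.** The Discussion lists a volunteer effect among the limitations, namely that physicians who favour incentives may be likelier to join. It then says: "we expect that the randomized control design of our study will limit the effect of this potential source of bias".

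**The concern.** Randomising sites makes the arms comparable, in expectation, for physicians who were already in the trial when the allocation was drawn. It does not do so for those who join later, unless neither they nor the people recruiting them can act on the allocation. This is a familiar route to bias in cluster trials.

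It deserves attention here because the intervention is personal income. The trait that the Discussion worries about, a favourable view of payment, could affect both who joins and how strongly that person responds. If late joiners at incentive sites were more responsive to payment than late joiners at control sites, the contrast between arms would mix the effect of the incentive with the effect of who was recruited. The Discussion's sentence makes no distinction between the two groups.

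**Working it through.** **1. The recruitment goal behind the late consents.** Power and sample size starts from five physicians per site, takes attrition R = 5.8% and inflates by 1/(1 − R)². This gives 5/(0.942)² = 5/0.8874 = 5.63, which rounds up to six, not the stated seven. Rounding up to seven would need R above 1 − √(5/6) = 8.7%. So the stated inputs do not reproduce the goal. It matters here only because the goal sets how many places were left to fill. At six per site, with five consented early, late recruits could be at most (72 − 60)/72 = 16.7%.

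**2. How many enrolled physicians may be late recruits.**

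- Minimum consented early: 12 × 5 = 60.
- If every site had exactly five early consenters and all were enrolled: 83 − 60 = 23, and 23/83 = 27.7%.
- If the two over-subscribed sites already had seven each: 23 − 4 = 19, and 19/83 = 22.9%.
- If every enrolled physician had consented early: 0%. This is a formal lower limit, since the text says that consent continued but gives no count.

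The 27.7% is a working ceiling rather than a strict one. The random draw at two sites, or replacement of an early leaver, could have removed someone who had consented early.

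**3. Whether the arm could have been known at consent.** Three statements have to be read together.

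- Participants learned their arm at the webinars. This suggests that disclosure followed consent, but late consents are not dated relative to the webinars.
- The allocating analyst was separate from recruitment. That protects the draw, but it does not tell us what the recruiters knew afterwards.
- Non-physicians were sought only at group-incentive sites, by invitation from the physicians, and the coordinating-center team consented them. Anyone aware of that step could infer that a site had a group incentive. Table 2 counts these staff as enrolled at the start of the intervention, so the step fell before or around the webinars. Its order relative to the late physician consents is not stated.

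Knowledge of the arm at consent is therefore neither established nor excluded.

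**4. What baseline data would absorb.** The first performance period precedes the incentive phase (Financial incentives), and Data analysis plans a repeated-measures longitudinal model. A stable difference in level between late recruits in different arms would largely cancel in a comparison of change. A difference in responsiveness to payment would not, because it appears only once payments begin.

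**5. Precision of an analysis restricted to early consenters.** For m physicians per site and intraclass correlation ρ, the variance of an arm mean is proportional to [1 + (m − 1)ρ]/m. The ICCs come from Power and sample size, and are taken as correlations between physicians within a hospital. Comparing m = 5 with m = 7:

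- ρ = 0.39: √(2.56/5) ÷ √(3.34/7) = 1.036, about 4% larger.
- ρ = 0.14: √(1.56/5) ÷ √(1.84/7) = 1.090, about 9% larger.

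Applying the stated 5.8% attrition to both sets gives m = 4.71 and m = 6.594. The ratios become √(0.5195/0.4825) = 1.038 and √(0.3226/0.2704) = 1.092.

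**The case against.** The strongest reply has four parts.

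- **Disclosure appears to follow consent.** The webinar sentence concerns people already enrolled, and the analyst was independent of recruitment. A reader might infer that up to 28% of the physicians were selected with knowledge of their arm. The documents do not support that: they do not show that any physician or recruiter knew the arm at consent. This part stands, and the point is limited accordingly. What remains is that recruiter masking is not stated and the timing of late consents is not given.
- **The Discussion claims little.** A reader might take it to say that randomisation removes the volunteer effect. It says only that the design limits it, and lists it as a limitation. For the 60 or more physicians consented before allocation, that is fair. The sentence needs a qualification, not withdrawal.
- **No size of bias follows.** A reader might multiply the share by a supposed difference, for example 23/83 × 10 points = 2.8 points. The 10 points have no source in the article, and the baseline period would largely absorb a difference in level. This also stands, so no shift is claimed.
- **A condensed article leaves detail elsewhere.** Recruiter procedures and sensitivity analyses may be set out in a full protocol or SAP that is not shown. This is fair as to their absence. It does not answer the point that the article states late recruitment and offers a reassurance that makes no exception for it.

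Restricting to early consenters also has a cost: five per site was the target before the allowance for attrition, so leavers take that set below the size used in the power calculation.

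**Conclusion.** The point holds as a limited one. Recruitment after allocation is stated outright. The share of enrolled physicians affected lies between 0% and about 28% (23 of 83), or about 23% if the two over-subscribed sites were full at randomisation. The upper figure assumes exactly five early consenters at every site, all of them enrolled; the text says at least five.

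Arm-related selection among these late recruits is possible but not shown. The form that matters is selection on responsiveness to payment, because adjustment for baseline performance would not remove it. The article gives no basis for putting a number on the resulting bias. The Discussion's reassurance is sound for physicians consented before allocation, and for later ones only if allocation was concealed from them and their recruiters.

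**What to change.** 1. Add a sensitivity analysis restricted to physicians consented before their site was randomised, and report it beside the full-set analysis. Discuss any disagreement as possible recruitment bias; the restricted result need not override the full one. If an SAP already contains this analysis, it only needs to be reported.
2. Report the numbers consented before and after randomisation by arm, and say whether recruiters and physicians could have known the allocation when late consents were taken.
3. Qualify the Discussion so that the reassurance applies to physicians consented before allocation, or after it with allocation concealed.

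The cost is one extra analysis using consent dates, which a consent process ordinarily records. Its standard error would be roughly 4% to 9% larger at five versus seven per site, and slightly more after attrition. The full-set analysis is unchanged.
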